###### Setting and Study Design

The study will be conducted in medical ICUs of three LAC DHS hospitals using a before-and-after study design. The study will be conducted sequentially among the three hospitals to allow investigators to modify and improve the implementation strategy over the course of the study based on clinician feedback (see Multimedia Appendix 1). For each hospital, we will collect preintervention data during the first 4 months and examine outcomes for a 4-month period after implementing the study intervention (see Multimedia Appendix 1). There are 52 medical ICU beds among the three hospitals. We anticipate that 960 patients will be admitted and screened in both the pre- and postintervention periods across the three medical ICUs. Based on our preliminary data, we estimate that 15% will be priority 3 and 4 patients who are candidates for intervention and 10% will be excluded due to lack of surrogate decision makers. As such, we estimate studying 130 patients during each 4-month period. Using alpha=.05 (two-sided), beta=.20 (80% power), and mean ICU stay of 6.5 days (SD 3.7) from our previous study [16], we expect to be able to detect a difference of 1.3 ICU days between time periods.

###### Time-Limited Trial Protocol

Physician-led family meetings will be conducted using a standardized protocol, which includes: (1) introductions, (2) summary of ICU course, (3) discussion of short- and long-term prognosis, (4) risks and benefits of aggressive ICU care, and (5) eliciting patients’ preferences for care during critical illness and/or at the end of life (see Multimedia Appendix 2 and Figure 1). Based on discussion of these elements, if patients and surrogate decision makers wish for a palliative approach, the patient will be transitioned to comfort-focused care. If patients and surrogate decision makers prefer aggressive ICU care, a TLT will be performed. For the TLT, care providers and surrogate decision makers will identify specific clinical parameters that will be used to determine whether patients are improving or worsening. Care providers will recommend a time period for which these parameters will be followed and likely actions to be taken at the end of the trial based on improvement or worsening. In the follow-up meeting, care providers will review trends in clinical parameters; they will also redefine prognoses based on these trends and additional clinical information obtained since the last meeting. Based on this information, recommendations regarding the next steps for care will be made. If the patients and surrogate decision makers opt for a palliative approach, comfort-focused care will be provided. If they prefer continuation of aggressive care, another TLT will be negotiated. This iterative process will be continued, with sequential meetings performed at the discretion of the ICU team (see Figure 1).

###### Multicomponent Implementation Strategy

Additional components to the implementation strategy are shown in Figures 1 and 2. ICU physicians—attendings and fellows—will be trained to use the TLT protocol in educational sessions utilizing actors as family members in role-playing scenarios (see Figure 2). Case managers will identify eligible patients each day by asking ICU physicians which admissions are ranked priority 3 or 4 and will schedule family meetings between care providers and patients and their families within 24 hours of admission. Family meetings will be conducted using checklists to improve compliance with the protocol (see Multimedia Appendix 2). A standardized electronic health record (EHR) template will be created to encourage documentation of important outcomes from meetings and to facilitate data collection. Each medical ICU will have a physician champion who will direct implementation of study protocols at each medical center and conduct monthly feedback sessions with ICU teams to discuss opportunities for improvement. Physician champions and research team members will meet every month to discuss strategies to improve family meetings, patient enrollment, and data collection.

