##### Experimental Approach

###### Study Population

Patients with a low likelihood of benefitting from ICU care due to advanced medical illnesses will be identified by assigning patients to priority levels from the Society of Critical Care Medicine guidelines for ICU admissions (see Table 1) [43-45]. This system prioritizes ICU admissions based on the projected likelihood of benefit. For this proposal, we will train all ICU physicians—attendings and fellows—to perform daily priority-level assessments for ICU patients. We have previously published our experience with training ICU teams to classify patients using this system [16]. Each day, case managers will ask ICU physicians to assign priority levels to each patient after ICU rounds. Our intervention will be implemented on all new ICU admissions who are assigned to priority levels 3 or 4. We will exclude patients who were assigned to different priority levels on admission but who are assigned to priority levels 3 or 4 during their ICU stay. If patients cannot communicate for themselves and do not have surrogate decision makers, they will be excluded.

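### Monthly work to improve patient enrollment is built into the strategy under test, so eligible admissions may be captured more completely after implementation than before: a risk of bias in ICU stay whose direction is unknown

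*Protocol article*

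**What the plan says.** Under Multicomponent Implementation Strategy, the article describes physician training, scheduling of family meetings, checklists, an electronic record template and local champions. In the same list it states that "Physician champions and research team members will meet every month to discuss strategies to improve family meetings, patient enrollment, and data collection". No study phase is attached to these meetings.

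Case finding appears in two places. Study Population states: "Each day, case managers will ask ICU physicians to assign priority levels to each patient after ICU rounds". Multicomponent Implementation Strategy states: "Case managers will identify eligible patients each day by asking ICU physicians which admissions are ranked priority 3 or 4". New admissions rated 3 or 4 form the cohort, and patients who reach those levels only later in their stay are excluded. The Limitations section concedes that the rating is subjective.

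Setting and Study Design gives each hospital a 4-month before window and a 4-month window after implementation, with hospitals taken in sequence. It adds: "We anticipate that 960 patients will be admitted and screened in both the pre- and postintervention periods across the three medical ICUs". About 130 patients are expected per period. Outcomes and Measurements has all outcomes collected in both periods by chart review on standardized forms. The Analysis Plan compares ICU days by an unadjusted rank-sum test and adds regression models with covariates that include severity of illness and hospital.

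**The concern.** A before-and-after comparison without a concurrent control relies on eligible patients being found in the same way in both windows. Here, improving enrollment is part of the strategy whose effect is being measured. Consent is waived for Aim 2, so enrollment most naturally means finding and registering eligible admissions.

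The article describes no way to recover a rating that was never given. With one rating a day after rounds, a patient who dies or leaves the ICU early is plausibly the easiest to miss. If such patients were missed more often before than after, the after cohort would hold more short stays. The primary outcome would then fall without any change in care, and life-support days and mortality could shift too.

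**Working it through.** **Inputs from the article (Setting and Study Design).** Two-sided alpha .05; 80% power; "mean ICU stay of 6.5 days (SD 3.7) from our previous study [16"; 960 screened per period; 15% eligible; 10% of those excluded.

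**The plan's own figures reproduce.**
- Cohort: 960 × 0.15 × 0.90 = 129.6, stated as 130.
- Detectable difference: (1.960 + 0.842) × 3.7 × √(2/130) = 1.29 days, stated as 1.3.

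There is no arithmetic error. The question is what uneven capture could do to a study of this size.

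**Assumptions not in the article.** The share of eligible patients missed in the before window, which patients these are, complete capture in the after window, and a gamma shape for ICU stay. Matching mean 6.5 and SD 3.7 gives shape (6.5/3.7)² = 3.09 and scale 6.5/3.09 ≈ 2.11.

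**Shift in the mean with no true effect.** If a fraction f of eligible before-window patients is missed and their mean stay is m, the before mean exceeds the after mean by

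f × (6.5 − m) / (1 − f).

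Under the gamma assumption, 6.3% of stays are under 2 days (mean 1.44 days) and 15.8% are under 3 days (mean 2.09 days). For example, missing 75% of stays under 3 days gives f = 0.75 × 0.158 = 0.1185, and the shift is 0.1185 × (6.5 − 2.09) / 0.8815 = 0.59 days.

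**Rank-sum rejection.** Simulated with 130 eligible patients per period, no true effect and two-sided 5%. Ranges are across repeat simulations of 4,000 to 20,000 runs.

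| Stays at risk of being missed before | Share of them missed | f | Shift (days) | Rejection rate |
|---|---|---|---|---|
| Under 2 days | 25% | 1.6% | 0.08 | 5–6% |
| Under 2 days | 50% | 3.2% | 0.17 | 7% |
| Under 2 days | 75% | 4.7% | 0.25 | 9–10% |
| Under 3 days | 25% | 4.0% | 0.18 | 7–8% |
| Under 3 days | 50% | 7.9% | 0.38 | 16–17% |
| Under 3 days | 75% | 11.9% | 0.59 | 33–36% |

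**Direction.** Take f = 10%:
- m = 2 days: 0.10 × 4.5 / 0.90 = 0.50 days, an apparent reduction after implementation.
- m = 6.5 days: zero.
- m = 10 days: 0.10 × (−3.5) / 0.90 = −0.39 days, an apparent increase after implementation.

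**Size against the target.** To imitate the full 1.3 days, f must equal 1.3 / (6.5 − m + 1.3). That is 19% for m = 1, 22% for m = 2 and 27% for m = 3. Losses of that size are well above any row of the table.

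**The case against.** The strongest reply is that the article never confines the monthly meetings to the after window. It expects the same number screened in both periods and collects all outcomes in both. With hospitals in sequence, better screening could also reach the before windows of later hospitals. This stands in part. A reader might infer that capture is improved only in the after cohort, and the text does not say so. But the equal screening numbers are a forecast and do not fix the procedure. Within any one hospital the before window always comes first, so gains that accumulate fall more on the after side.

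A reader might also infer that the two descriptions of case finding conflict. They do not: asking which admissions are ranked 3 or 4 presupposes that ranks have been assigned, so the two are compatible.

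A third inference would be that better data collection distorts the primary outcome. ICU stay comes from chart review on standardized forms in both periods, so that part carries little weight. The risk lies in who enters the cohort.

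Finally, the short-stay direction is assumed, and a patient who stays close to three days would usually meet more than one daily rating. The rows for stays under 2 days are therefore closer to the likely mechanism, and they show rejection only modestly above 5%. The planned severity adjustment may absorb some of any imbalance, although the rank-sum comparison itself is unadjusted.

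**Conclusion.** The point holds as a risk that the article leaves open. Improvement of enrollment belongs to the strategy being evaluated, entry rests on a once-daily subjective rating, and nothing in the article holds the screening procedure constant across a hospital's two windows.

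If the patients missed before are mainly short-stay, the spurious reduction is about 0.1 to 0.25 days when losses are confined to stays under 2 days (rejection about 6% to 9%). It is about 0.2 to 0.6 days when losses extend to all stays under 3 days (about 7% to 34%). These figures rest on the gamma shape, on 25% to 75% of such stays being missed before, and on none being missed after. None of these is in the article.

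The stronger conclusion, that the design will shorten apparent ICU stay, is not supported: misses with average stays give no bias and misses with long stays reverse the sign.

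**What to change.** State that at each hospital one screening procedure, with every new admission rated daily as Study Population describes, runs unchanged from the first day of the before window to the last day of the after window. Make changes to screening only between hospitals. Report, by hospital and period, the number of admissions, admissions rated and admissions never rated, so that readers can see whether capture differed.

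The cost is a few sentences and counts from the screening log. The drawback is that a capture problem found within a hospital's windows is not corrected until the next hospital.

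An analysis restricted to patients still in the ICU at 72 hours may look like a natural check, but it should not be used. Family meetings are scheduled within 24 hours of admission and can lead to comfort-focused care, so remaining in the ICU at 72 hours can itself be changed by the intervention. A different result in that subset could not be attributed to capture.

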###### Outcomes and Measurements

All outcomes will be collected in both the pre- and postintervention periods. The primary outcome will be ICU length of stay. Secondary outcomes will include hospital length of stay, days receiving life-sustaining treatments (eg, mechanical ventilation, use of vasopressor medications, and renal replacement therapy), number of attempts at cardiopulmonary resuscitation (CPR), number of invasive procedures (eg, central venous or arterial catheterization, thoracentesis, paracentesis, lumbar puncture, and endoscopy), and outcomes of hospitalization (eg, death, discharge to hospice, skilled nursing facility, or home). These data will be collected from retrospective chart review by trained case managers using standardized data abstraction forms.

###### Analysis Plan

Primary and secondary outcomes will be compared before and after the intervention [46-48]. Days in ICU, days in hospital, and days receiving life-sustaining treatments will be compared using Wilcoxon rank-sum tests [49,50]. ICU and hospital mortality rates will be compared using χ^2^ tests. Other continuous and categorical outcomes will be compared between groups using *t* tests or χ^2^ tests, respectively, or equivalent nonparametric approaches for variables that are nonnormally distributed. Multivariable regression models will be used to examine the effects of covariates, such as patient demographics, comorbid conditions, severity of illness, and hospitals, on study outcomes [49,50]. Primary and secondary outcomes before and after the intervention will also be analyzed and will be stratified by ICU survivors and nonsurvivors. Days receiving ICU care, days receiving life-sustaining treatments, number of invasive procedures, and number of CPR attempts among patients who did not survive hospitalization will be considered nonbeneficial treatment and will be compared before and after the intervention.

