#### Intensive Care Unit Overutilization in the Los Angeles County Department of Health Services

Like many health care systems, ICU overutilization is highly prevalent in the hospitals of the Los Angeles County (LAC) Department of Health Services (DHS), the second-largest public health care system in the United States. A recent study from our group showed that among 808 medical ICU patients at Harbor-UCLA Medical Center (HUMC), over 20% had reduced likelihoods of benefit from ICU care due to advanced medical illnesses, such as advanced dementia and metastatic cancer (see Table 1) [16]. Of these patients, 86% died or were discharged in severely compromised health states and only 6% were discharged home. This subset of patients is at the highest risk to have invasive treatments that prolong suffering without improving outcomes. As such, we focus this proposal on improving ICU utilization on these critically ill patients with advanced medical illnesses.

In order to understand why patients with advanced medical illnesses received ICU care so frequently, we conducted semistructured interviews of ICU physicians and nurses at LAC DHS hospitals. Key themes that emerged from these interviews were that health care providers do not comprehensively discuss prognoses, risks and benefits, and patient preferences for ICU treatments, which lead to inaccurate expectations from ICU care and unrealistic fears of prematurely forgoing potentially beneficial treatments. Barriers to effective shared decision making included (1) underappreciation of the value of ICU care planning, (2) lack of institutional standards and tools for ICU care planning, and (3) difficulty in scheduling meetings between providers and families.

**Table 1 table1:** Priority levels of medical intensive care unit (ICU) admissions at Harbor-University of California Los Angeles Medical Center.

Priority	Description	Percentage, %
1	Critically ill, needing intensive treatment and monitoring that cannot be provided outside of ICUs	46.9
2	Not critically ill, but requiring close monitoring and potentially immediate intervention	23.4
3	Critically ill, but reduced likelihood of recovery because of underlying diseases or severity of acute illness	20.9
4	Not appropriate for ICU; equivalent outcomes achievable with non-ICU care	8.8

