**Figure 1 figure1:**
[figure not shown]
Implementation strategy for time-limited trials. ICU: intensive care unit.

We hypothesize that a multicomponent quality-improvement intervention, informed by stakeholder input and that uses protocoled TLTs as the default ICU care-planning approach for critically ill patients with advanced medical illnesses, will decrease the duration and intensity of nonbeneficial ICU care without changing hospital mortality. We will examine our hypothesis with the specific aims discussed in the following sections.

#### Aim 1

Aim 1 consists of identifying barriers and facilitators to performing TLTs in ICU patients with advanced medical illnesses using focus groups of physicians and semistructured interviews of patients and their families.

#### Aim 2

Aim 2 consists of examining whether a multicomponent quality-improvement intervention using TLTs as the default care-planning approach for ICU patients with advanced medical illnesses reduces duration and intensity of nonbeneficial ICU treatments

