###### Expected Results

We expect to find fewer ICU days, hospital days, and days of life-sustaining treatments after the TLT intervention. We also expect a fewer number of attempts at CPR and other invasive procedures. We expect mortality rates to remain unchanged before and after the intervention. We expect reductions in ICU days, days receiving life-sustaining treatments, and number of invasive procedures after the intervention to be greater among patients who died during hospitalization than among survivors.

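### The pooled test on ICU days cannot separate earlier ICU death from earlier live ICU discharge, and the planned survivor strata and mortality tests close that gap only in part

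*Protocol article*

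**What the plan says.** All references are to the Protocol article.

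- Outcomes and Measurements: "The primary outcome will be ICU length of stay". No rule is given for a stay that ends in death.
- Analysis Plan, main comparison before versus after: "Days in ICU, days in hospital, and days receiving life-sustaining treatments will be compared using Wilcoxon rank-sum tests".
- Analysis Plan, mortality: "ICU and hospital mortality rates will be compared using χ^2^ tests".
- Analysis Plan, strata: "Primary and secondary outcomes before and after the intervention will also be analyzed and will be stratified by ICU survivors and nonsurvivors".
- Analysis Plan, hospital deaths: ICU days and other treatments "among patients who did not survive hospitalization will be considered nonbeneficial treatment and will be compared before and after the intervention".
- Objectives, hypothesis: the intervention "will decrease the duration and intensity of nonbeneficial ICU care without changing hospital mortality".
- Expected Results: reductions are expected "to be greater among patients who died during hospitalization than among survivors".
- Background, on the target population: "Of these patients, 86% died or were discharged in severely compromised health states and only 6% were discharged home". Death is not reported separately from compromised discharge.

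**The concern.** A rank test on raw ICU days looks only at how long the stay lasted, not at how it ended. A death on day 2 ties with a live transfer on day 2 and ranks as a shorter stay than a recovery on day 6. Death is likely to be a common way out of the ICU in this population. The intervention also acts on that route, because the Time-Limited Trial Protocol section provides for a move to comfort-focused care when patients or surrogates prefer it.

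A reader of a positive primary result will want to know what changed: earlier death in the ICU, earlier transfer out of the ICU to die elsewhere, or earlier recovery. The survivor and nonsurvivor strata are the natural place to look. They are defined by an outcome that the intervention can alter, so a shorter stay among ICU survivors need not mean that anyone recovered faster.

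**Working it through.** **Inputs.** From Setting and Study Design: mean ICU stay 6.5 days, SD 3.7, 130 patients per period, two-sided alpha 0.05, 80% power, detectable difference 1.3 days. Assumed, because the article does not give them: ICU mortality, lognormal stays, and equal stay distributions in survivors and nonsurvivors before the intervention.

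**1. The plan's own figures.** Accrual: 960 × 0.15 × 0.90 = 129.6, about 130. Detectable difference = SD × (z₀.₉₇₅ + z₀.₈₀) × √(2/n) = 3.7 × (1.960 + 0.842) × √(2/130) = 1.286, which rounds to 1.3. Both reproduce.

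**2. Stable strata.** If ICU mortality *p* is the same in both periods and the same kinds of patients die, then overall reduction = *p* × (reduction in nonsurvivors) + (1 − *p*) × (reduction in survivors). With no change in survivors, 1.3 days overall needs deaths to come earlier by 1.3/*p*:

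| Assumed ICU mortality | Shift in time to death |
|---|---|
| 40% | 3.25 days |
| 50% | 2.6 days |
| 60% | 2.17 days |

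Simulated rejection rates with 130 per period, *p* = 50% and the same 1.3-day overall reduction (3,000 runs each):

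| Test | Only deaths earlier | Only live discharge earlier |
|---|---|---|
| Pooled Wilcoxon | 94.5% | 94.2% |
| Mortality χ² | 5.1% | 5.6% |
| Wilcoxon, nonsurvivors | 100% | 5.0% |
| Wilcoxon, survivors | 5.4% | 99.9% |

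At 30% and 70% mortality the pooled test stays at 93–95% on either route. It does not distinguish the routes, and the mortality test does not register timing. The strata do distinguish them here.

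**3. Strata changed by the intervention.** Let a share *q* of patients who would have died in the ICU leave it for comfort-focused care, with their ICU stay shortened by a fraction *r*. Nobody else changes.

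- Fall in mean ICU-survivor stay = *p q r* × 6.5 / (1 − *p* + *p q*).
- Fall in mean ICU-nonsurvivor stay = 0.
- Whole-cohort fall = *p q r* × 6.5.

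With *p* = 0.5, *q* = 0.5, *r* = 0.7:

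- Whole cohort: 0.5 × 0.5 × 0.7 × 6.5 = 1.14 days.
- ICU survivors: 1.1375 / 0.75 = 1.52 days.
- Simulated Wilcoxon rejection: 90–91% in ICU survivors and 5–6% in ICU nonsurvivors, over two separate simulations.

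With *q* = 0.3, *r* = 0.5: survivors 0.4875 / 0.65 = 0.75 days, and the survivor stratum rejects in 35% of runs.

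Range over *p*, keeping *q* = 0.5 and *r* = 0.7: at *p* = 0.3 the survivor fall is 0.6825 / 0.85 = 0.80 days; at *p* = 0.7 it is 1.5925 / 0.65 = 2.45 days.

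**4. What the other planned analyses show in case 3.** With *p* = *q* = 0.5, ICU mortality falls from 50% to 25%. Power of the χ² test is about Φ[(0.25 − 1.96 × √(2 × 0.375 × 0.625/130)) / √((0.25 + 0.1875)/130)] = Φ(2.28) = 0.99, so a change in who is in the strata would be visible. What follows depends on where these patients go:

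- *They die on a ward.* Hospital mortality is unchanged, and the hospital-nonsurvivor comparison picks up their shorter ICU stays.
- *They go to hospice.* Outcomes and Measurements counts this as a discharge. They drop out of the hospital-nonsurvivor comparison and hospital mortality falls too, which can look like better survival. More hospice discharges would appear in the disposition outcome, but nothing planned links them to ICU days.

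**5. Can stable strata be confirmed from the mortality tests?** Not reliably. With 130 per period and baseline mortality of 20–70% (assumed), power to detect a 10-point rise is 37–46%.

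**The case against.** The strongest case against the point is that the plan already answers it. The sentences after the Wilcoxon statement add survivor and nonsurvivor strata, a hospital-nonsurvivor comparison, and tests of both ICU and hospital mortality. When mortality is stable, the overall difference is the mortality-weighted sum of the two stratum differences, so the contribution of earlier death can be read from planned outputs. This stands. A reader might infer that the plan as a whole cannot tell earlier death from earlier recovery; the Analysis Plan does not support that, and step 2 shows the strata separating the routes cleanly.

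It can also be said that shorter stays before death are the stated target. This stands as well. The hypothesis, the definition of nonbeneficial treatment and the Expected Results all say so. A reader might infer that the endpoint hides a harm behind a favourable number, but the documents declare this direction openly.

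Finally, the article is condensed and an added display could sit in an analysis plan that is not shown. That limits the weight of the point. The article does, however, name the survivor strata as a way to read the primary outcome, and that reading is open to the error in step 3. The objection covers stable strata only; it does not cover strata whose membership the intervention changes.

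**Conclusion.** The point holds in limited form. The pooled primary test does not separate the routes out of the ICU. The planned supporting analyses do so if the same kinds of patients remain in each stratum, and only partly if comfort-focused care moves dying patients out of the ICU. In that case the ICU-survivor stratum can show a stay shorter by about 0.8 to 2.5 days (ICU mortality 30–70%, half of those patients leaving, stays 70% shorter) with no faster recovery at all. Under the milder pattern at 50% ICU mortality it shows about 0.75 days.

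These sizes rest on assumed mortality, assumed movement out of the ICU and lognormal stays. They illustrate the mechanism and do not estimate what happened in this study. The issue is attribution of the effect. It does not invalidate the primary outcome, and the remedy is a worthwhile, inexpensive improvement.

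**What to change.** Keep ICU length of stay as primary and keep every planned analysis. Add, for all eligible patients and for each period, the cumulative incidence from ICU admission of two competing events: ICU discharge alive and death in the ICU. Split live ICU discharge by final hospital disposition, with in-hospital death or hospice in one group and all other discharges in the other. State in advance that a shorter stay will be interpreted by which curve moved, and that a shorter stay in the survivor stratum will not by itself be read as faster recovery.

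**Cost.** One additional analysis and a few lines of text, with a possible need to qualify the headline. ICU days, ICU deaths and hospital disposition are already needed for the planned comparisons. Splitting live discharge by the care plan at ICU exit would be sharper but should be optional: Outcomes and Measurements does not list that item, and the meeting template in the health record belongs to the intervention, so preintervention patients may need extra chart abstraction.

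### ICU length of stay is compared between two non-randomised periods by an unadjusted rank-sum test, and the planned regression is not designated to give an adjusted before/after effect as the primary result

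*Protocol article*

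**What the plan says.** All of this is in the Protocol article, Methods, Aim 2.

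- **Outcome** (Outcomes and Measurements): "The primary outcome will be ICU length of stay".
- **Design** (Setting and Study Design): "The study will be conducted in medical ICUs of three LAC DHS hospitals using a before-and-after study design". Timing is set per site, relative to the start of the intervention there: "For each hospital, we will collect preintervention data during the first 4 months and examine outcomes for a 4-month period after implementing".
- **Test** (Analysis Plan): "Days in ICU, days in hospital, and days receiving life-sustaining treatments will be compared using Wilcoxon rank-sum tests". No stratification or covariate is attached to it.
- **Regression** (Analysis Plan): "Multivariable regression models will be used to examine the effects of covariates, such as patient demographics, comorbid conditions, severity of illness, and hospitals". The models apply to the outcomes of the study. The section does not say that these models yield the before/after effect, or which analysis carries the primary conclusion.
- **Sizing** (Setting and Study Design): "Using alpha=.05 (two-sided), beta=.20 (80% power), and mean ICU stay of 6.5 days (SD 3.7) from our previous study", with about 130 patients per period, "we expect to be able to detect a difference of 1.3 ICU days between time periods".
- **Selection** (Limitations): the priority rating that determines eligibility is acknowledged to be subjective. If numbers fall short, patients who reach priority 3 or 4 only after admission may be added, which would make a further 10% of ICU patients eligible.

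**The concern.** Without randomisation, a crude comparison of periods estimates the intervention effect only if the patients in the two periods are alike. The document itself gives two ways in which they may not be.

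1. **The rating can move with period.** ICU physicians assign priority 3 or 4 knowing which period they are in. After implementation, that rating leads to a family meeting being scheduled within 24 hours of admission (Multicomponent Implementation Strategy). The threshold for giving it could shift in either direction.
2. **The criteria can widen.** Against a base of 15% eligible, a further 10% would make the added patients 10/(15 + 10) = 40% of the eligible pool. If the two periods were affected unequally, their case mix would differ.

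A rank-sum test on ICU days cannot separate such a difference from the intervention. A drift towards shorter stays would look like benefit, and a drift the other way would hide it. The plan already names the covariates that could help, but does not give the adjusted estimate the leading role. If crude and adjusted results disagreed, the text does not say which one the conclusion rests on.

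**Working it through.** **1. The plan's own figures reproduce.** Inputs are from Setting and Study Design; 960 is read as the number screened in each period.

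- Patients per period: 960 × 0.15 × (1 − 0.10) = 129.6, about 130.
- Standard error of the difference: 3.7 × √(2/130) = 0.459 days.
- Detectable difference: (1.960 + 0.842) × 0.459 = 1.29, about 1.3 days. Power for 1.3 days is 80.9%.
- Allowing for the rank-sum test's efficiency under normality (3/π = 0.955): detectable difference 1.32 days, power for 1.3 days 79.0%.

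**2. What drift does to the crude test.** The documents give no hospital-level stays and no drift data, so every shift below is an assumption. Set-up: 130 per period, no intervention effect, gamma-distributed stays with coefficient of variation 3.7/6.5 = 0.569, two-sided 0.05, 3,000 simulated studies per row. The crude rank-sum test is set beside one stratified by hospital (van Elteren).

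Severity drift, the same in every hospital:

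| Stays shorter by | False difference (days) | Crude rejects | Hospital-stratified rejects |
|---|---|---|---|
| 5% | 6.5 × 0.05 = 0.33 | 10.1% | 10.1% |
| 10% | 6.5 × 0.10 = 0.65 | 29.2% | 28.8% |
| 20% | 6.5 × 0.20 = 1.30 | 84.2% | 83.6% |

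Hand check of the 10% row by normal approximation: 0.65/0.459 = 1.416, and Φ(1.416 − 1.960) = Φ(−0.544) = 29%.

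Hospital-mix shift: equal shares before, then 10 points of share move from the longest-stay to the shortest-stay hospital.

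| Hospital means (days) | False difference (days) | Crude rejects | Hospital-stratified rejects |
|---|---|---|---|
| 6.5 ± 1 | 0.10 × 2 = 0.2 | 6.6% | 4.6% |
| 6.5 ± 2 | 0.10 × 4 = 0.4 | 11.4% | 5.4% |
| 6.5 ± 3 | 0.10 × 6 = 0.6 | 21.2% | 5.4% |

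With the mix unchanged, the crude test rejects in 4.9% to 5.1% of studies for all three sets of means.

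**3. Reading the tables.** A 20% severity drift equals the whole 1.3-day design target. Stratifying by hospital repairs the hospital-mix error and leaves the severity error untouched; only adjustment for severity can address that.

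**The case against.** The strongest reply is that adjustment is already planned, on the very factors at issue. The regression sentence names severity and hospitals and applies to study outcomes, which include ICU days. It stands in a section that opens by announcing before/after comparisons, so a model with a period term is the sensible reading. That much stands. A reader might infer that the plan ignores case mix, or that its regression leaves period out; the text supports neither. What remains is that "Multivariable regression models will be used to examine the effects of covariates" states a different purpose, and no adjusted period effect is put forward as the main result.

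Two further inferences go beyond the text. The Analysis Plan does not call the rank-sum test primary, and does not say that hospitals are pooled. Both are inferred from its being the only before/after test named for ICU days and from the single 130-per-period calculation.

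It can also be said that each hospital supplies equal 4-month windows and so serves as its own comparison. This stands: it weakens the hospital-mix route, and nothing in the document points to a systematic shift between hospitals. Selection and severity are the stronger routes.

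Finally, a condensed article may leave model form and error structure to a fuller plan. I agree, and raise neither. The point concerns the test the article does name for its primary outcome and the role it gives the regression.

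**Conclusion.** The concern holds in a limited form. The primary outcome is to be compared by a test that takes no account of case mix, in a non-randomised design whose selection process can change between periods. The adjusted analysis that would answer the question better is planned but not designated.

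The size depends on drifts that the documents do not quantify. Under the assumptions above, a 10% severity drift gives about 29% false rejection and a 10-point hospital-mix shift with means of 6.5 ± 2 days gives about 11%. These are illustrations, not predictions, and they do not show that case mix will in fact drift. The sample-size calculation is sound and needs no change.

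**What to change.** Amend the Analysis Plan so that the primary result is the period effect from the regression of ICU days already planned, adjusted for hospital and for prespecified admission covariates (severity, comorbidity, demographics). Report it as a difference in days with a 95% CI, the scale on which the study was sized; if a log link is chosen, derive the difference in days from the model. Keep the rank-sum test as an unadjusted supporting analysis. A hospital-stratified rank test is an optional sensitivity analysis, with the stated limit that it handles hospital mix and not severity.

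The cost is mainly wording, since the Analysis Plan already names these covariates. Outcomes and Measurements describes the collection of outcomes only, so it should be confirmed that the chart abstraction also captures admission severity and comorbidity. The downside is dependence on a model form. No adjustment removes unmeasured time trends, and the report should say so.
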